### Study design

This trial will be done in accordance with the guidelines laid down in the Declaration of Helsinki (1964). The study has already been approved by the bioethics committee of the Tehran University of Medical Sciences (no. IR.TUMS.VCR.REC.1395.1683). At the initial phase, we will screen 300 NAFLD patients, based on the inclusion criteria mentioned above. Those who meet the criteria will be included. All participants will be asked to complete and sign the written informed consent. Before allocating participants into the vitamin D and placebo groups, anthropometric indices, including weight, height, and waist circumference (WC), will be measured and body mass index (BMI) will be calculated. Individual questionnaires including demographic characteristics, past medical, drug and diet history, as well as socioeconomic status (SES) will be completed for each patient through the comprehensive face-to-face interview. To perform biochemical and molecular measurements, 10-mL overnight fasting venous blood samples will be obtained from each patient. All individual information of participants will be secret. A diagram of study design was shown in Fig. 1.

**Fig. 1 Fig1:**
[figure not shown]
*Diagram* of the study design

### Randomization

Forty-six patients will be enrolled in the whole project. We will use block randomization, in which the assignment will be done based on sex (male/female) and BMI (overweight/obese). Participants will be matched based on sex and BMI into blocks. Therefore, the block size would be four [14, 15]. This method of randomization will provide the equal number of men and women as well as overweight and obese patients that will be assigned to the intervention and placebo groups [14, 15]. Random allocation sequence will be generated using Random Allocation Software: RAS [16]. Given the total sample size of 46 and considering matched cases in terms of sex and BMI, the sample size in each subgroup of gender and BMI will be 12 ± 1. The allocation process of participants into vitamin D and placebo groups will be carried out using computer-generated random sequences by a third person who will not be involved in the project directly.

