## Methods/design

### Participants

This parallel randomized double-blind placebo-controlled clinical trial (RCT) will be done on patients with NASH. Patients will be recruited from the Masoud Internal Specialized Clinic and Imam Khomeini Hospital, affiliated with Tehran University of Medical Sciences, Tehran, Iran. We calculated required sample size based on data from a previous study [12] by considering serum laminin as a key dependent variable, type I error of 0.05, and study power of 90%. Considering the mean difference in serum laminin levels of 136.7 ng/mL between the two groups [12], based on the suggested formula for parallel clinical trials, we reached the sample size of 18 patients in each group. Taking into account a possible drop-out rate of 30%, 23 patients will be enrolled in each group. The study is registered in the Iranian Registry of Clinical Trials website (http://www.irct.ir, identifier: IRCT201405251485N13). This study was reported based on recommended check lists for clinical trials (Additional files 1 and 2).

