### Inclusion criteria

In this study, we will recruit NAFLD patients with NASH aged 20–60 years, at least six months before enrollment in the study. Diagnosis of fatty liver will be made based on findings from ultrasound reports. Patients will be recruited if they had NAFLD at grade 2 or 3. Having a vitamin D deficiency or insufficiency (serum levels of 25 (OH) vitamin D_3_ < 30 ng/mL) would be another requirement for inclusion in the study [13].

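### The randomisation strata cover only overweight and obese patients although eligibility sets no BMI limit, and the block wording neither settles the scheme nor by itself yields 12 ± 1 per cell

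*Protocol article*

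**What the plan says.** All references are to the protocol article.

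- **Strata.** Under Randomization, "the assignment will be done based on sex (male/female) and BMI (overweight/obese"). No other BMI class is named.
- **Blocks.** The same section continues: "Participants will be matched based on sex and BMI into blocks. Therefore, the block size would be four".
- **Balance.** It then says: "This method of randomization will provide the equal number of men and women as well as overweight and obese patients". That sentence goes on to refer to assignment to the intervention and placebo groups.
- **Cell size.** From the total of 46 and the matching on sex and BMI it concludes that "the sample size in each subgroup of gender and BMI will be 12 ± 1".
- **Eligibility.** Inclusion criteria give an age range, a vitamin D threshold and an ultrasound grade ("Patients will be recruited if they had NAFLD at grade 2 or 3"). Exclusion criteria list many conditions and drugs. Neither section mentions BMI.
- **Entry.** Study design says that 300 patients will be screened and that those meeting the criteria will be included. BMI is calculated before allocation but is not named as a filter. No quota by sex or BMI is stated.
- **Analysis.** Statistical analysis names the baseline value of each outcome as covariate, and no other covariate.

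**The concern.** Two stated rules do not fit together. The eligibility rule admits patients of any BMI, while the allocation rule has places only for those who are overweight or obese. An article may leave detail to a fuller protocol, but this one gives both rules itself and they conflict.

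The description of the blocks is also unsound. Strata are the groups within which patients are randomised. Block length is the number of consecutive patients over which the arms are forced to balance, and it is a free choice. The word *therefore* derives a length of four from matching. The only four in sight is the number of sex-by-BMI cells (2 × 2), so strata and block length appear to have been confused. A reader cannot tell which scheme was run, and the two schemes that the words allow have different properties.

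Finally, blocking governs how a cell is split between arms, not how many patients enter the cell. The cell size is stated as a consequence of the method, but it would need control of enrolment.

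**Working it through.** **Inputs from the article.** Total 46 ("Forty-six patients will be enrolled in the whole project"), 23 per arm ("Taking into account a possible drop-out rate of 30%, 23 patients will be enrolled in each group"), 2 × 2 = 4 cells, block size 4, stated cell size 11 to 13. The sex and BMI mix of eligible patients is not given, so it is varied below as an assumption.

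**1. The stated cell size.** 46 / 4 = 11.5, which lies within 12 ± 1. The figure is reproduced if the four cells are equal. The only sets of four sizes between 11 and 13 that sum to 46 are (11, 11, 12, 12) and (11, 11, 11, 13).

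**2. Reading A: separate blocks of four within each stratum, no quota.** Cell sizes are then multinomial with N = 46. For four equally common cells:

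P(all cells 11 to 13) = 6 × 46! / (11!² 12!²) × 0.25⁴⁶ + 4 × 46! / (11!³ 13!) × 0.25⁴⁶ = 0.0182 + 0.0112 = 0.029.

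The factors 6 and 4 count the ways of placing each set of sizes in the four cells. For other assumed mixes, with sex and BMI independent:

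| Sex split | BMI split | Expected cells | P(all 11 to 13) |
|---|---|---|---|
| 50/50 | 50/50 | 11.5, 11.5, 11.5, 11.5 | 2.9% |
| 60/40 | 50/50 | 13.8, 13.8, 9.2, 9.2 | 1.2% |
| 60/40 | 60/40 | 16.6, 11.0, 11.0, 7.4 | 0.5% |
| 70/30 | 60/40 | 19.3, 12.9, 8.3, 5.5 | 0.03% |

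Arm balance under this reading is good. Only the last, incomplete block of a stratum can be unbalanced. A remainder of 1 or 3 patients leaves a difference of 1, and a remainder of 2 leaves at most 2. With cells of 11, 12 or 13 the difference is at most 1 per cell.

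**3. Reading B: each block holds one patient from each cell, split 2:2.** Eleven such blocks use 44 patients, so cells of 11 to 12 follow by construction. Sex is not balanced between arms, however. Of the 6 possible orders in a block, 2 put both men in the same arm, and another 2 put both obese patients in the same arm.

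- The number of men in one arm per block is 0, 1 or 2 with probabilities 1/6, 4/6 and 1/6, so its variance is 1/3.
- Over 11 blocks (22 men) the variance is 11/3 = 3.67, SD 1.91. Simple randomisation of 22 men gives 22 × 0.25 = 5.5, SD 2.35.
- P(equal men in both arms) = 21%. P(arms differ by 4 or more men) = 43%, against 52% under simple randomisation.

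**4. Patients without a stratum.** The article gives no share of eligible patients below overweight. If that share is q, the expected number among 46 is 46q, and P(at least one) = 1 − (1 − q)⁴⁶.

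| Assumed q | Expected of 46 | P(at least one) |
|---|---|---|
| 2% | 0.9 | 61% |
| 5% | 2.3 | 91% |
| 10% | 4.6 | 99% |

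**The case against.** The strongest reply is that the scheme is ordinary stratified blocking, loosely worded. Assignment by sex and BMI describes stratification, and matching into blocks fits blocks of like patients. Read in full, the balance sentence concerns numbers assigned to the two arms, and blocks of four within strata deliver that closely. The cell size is stated on the premise of matched cases, and with 300 screened for 46 places enrolment could be matched so that 12 ± 1 is met. The multinomial model would then not apply. BMI is known before allocation, so overweight or obese may act as an unwritten entry limit.

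Much of this stands:

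- A reader might infer that the method cannot deliver its promises or that arm balance is lost. The document does not support that. Under the within-stratum reading the arms are well balanced, and with a quota the cell sizes are attainable.
- The balance sentence should be reworded, not deleted.
- The 43% applies only to the one-per-cell reading, which is the less natural one. Even there the variance falls by a third (5.5 to 3.67).
- A reader might also take the Discussion to claim sex and BMI balance as a strength. It praises the block randomisation method and does not mention that balance.
- Nothing in the text shows that any patient was allocated ad hoc.

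What the reply does not remove is that no BMI limit and no quota are written down, that the entry rule as written speaks against both, and that block length does not follow from matching.

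**Conclusion.** The point holds in a limited form. As written, the allocation rule does not cover every eligible patient. How many patients this affects cannot be known from the document: under assumed shares of 2% to 10%, about 1 to 5 of 46. The block description does not identify the scheme, and neither of the two readings above by itself gives both balanced arms and 12 ± 1 per cell.

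The figure of about 3% rests on two assumptions: recruitment without a quota, and four equally common cells. The second is the favourable case among the mixes tried, and less even mixes give smaller probabilities. If a quota was in force, the criticism reduces to its not being stated.

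The defect lies in the definition of the strata, the account of the blocks and the cell-size statement. It does not show that the comparison between arms is biased. It should be corrected because the rules conflict and the correction is cheap.

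**What to change.** 1. Make the strata exhaustive: cut BMI at < 30 versus ≥ 30 kg/m², so that every eligible patient has a stratum. Alternatively, state the BMI entry limit under Inclusion criteria.
2. Describe separate permuted-block sequences within each of the four sex-by-BMI strata, and remove the derivation of block size from matching.
3. Reword the balance sentence to say that numbers are balanced between arms within each stratum.
4. Drop 12 ± 1, or state the enrolment quota behind it.
5. Trial status expected recruitment to be completed by 15 January 2019, and the article appeared on 4 March 2019. If recruitment has ended, the list cannot be changed. Report the scheme actually used, including how any patient below overweight was handled.
6. Add sex and BMI class as covariates to the Statistical analysis model, since they are randomisation factors and the model now names only the baseline outcome value.

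The cost is a text correction and two degrees of freedom for sex and BMI class as main effects, or three for a four-level stratum factor. If patients are still to be allocated, the remaining sequences would also have to be regenerated in the software already named.

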### Intervention

All patients, researchers, gastroenterologist, statistical analyst, and laboratory staff will be blind to intervention. According to the protocol of vitamin D deficiency and insufficiency treatment [13], the supplementation procedure for vitamin D will be set at a 4000 IU tablet per day for 12 weeks. The experimental group will receive 4000 IU vitamin D supplements daily with their main meals for 12 weeks. The placebo group will take placebo tablets containing lactose, which are similar to vitamin D tablets in appearance, shape, color, and smell. Participants in the placebo group will also be requested to take the tablet with their main meals for 12 weeks. The vitamin D and placebo tablets will be produced by the PARS MINOO Co., Tehran, Iran. The quality control of vitamin D tablets will be determined by the HPLC method. All patients will be blind for grouping till the end of the trial. A third person that is not involved directly in the study will package the vitamin D and placebo tablets in the bottles. The bottles will be coded as A and B and will remain unknown to researchers until the end of study. Patients will take their bottles in two time periods: at their first visit and in the middle of trial at week 6 in the laboratory of Cellular and Molecular Nutrition.

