### Adherence

To determine the adherence to the intervention, individuals will be asked to record their daily consumption of supplements or placebos in a checklist given them by the investigators. To increase compliance and avoid forgetting the use of supplements and placebos, participants will receive messages on their cell phones every day from the investigators’ side. In addition, we will examine serum vitamin D levels at study baseline and at the end of the trial as a measure of compliance.

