### Statistical analysis

Statistical analyses of all data will be performed using SPSS software version 21.0 (SPSS Inc., Chicago, IL, USA). The intention-to-treat approach will be used for data analysis. Data will be expressed as mean ± standard deviations (±SD). The one-sample Kolmogorov–Smirnov test will be used for assessing the normality of the distribution of data. In case of non-normal distribution of a variable, we will apply the log transformation. If the variables were non-normally distributed even, after log transformation, we will use non-parametric tests in the analyses. Repeated measure analysis of variance will be used to identify the effect of the intervention of outcome variables. In these analyses, baseline levels of the outcome variables will be considered as covariates. If any outcome variable was non-normally distributed, we will use the Friedman test. *P* < 0.05 will be considered statistically significant. All analyses will be done by a blind researcher before uncoding the study interventions.

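### One letter per arm on the bottles means a single identification unblinds all 46 patients, and comparing end-of-trial vitamin D under those letters will probably unblind the analyst

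*Protocol article*

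**What the plan says.** All places are in the protocol article.

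- **Intervention:** patients, researchers, the gastroenterologist, the statistical analyst and laboratory staff are all to be blind. A third person packs the tablets. "The bottles will be coded as A and B and will remain unknown to researchers until the end of study". Patients collect bottles twice, at the first visit and at week 6, in the study laboratory.
- **Randomization:** blocks are formed within sex (two levels) and BMI (two levels). "Therefore, the block size would be four". With 46 patients, "the sample size in each subgroup of gender and BMI will be 12 ± 1". Allocation is made "by a third person who will not be involved in the project directly".
- **Participants:** 18 patients per group are required, and "23 patients will be enrolled in each group" to allow for drop-out.
- **Adherence:** "we will examine serum vitamin D levels at study baseline and at the end of the trial as a measure of compliance". The Outcomes section repeats that vitamin D and calcium are measured at both times, outside the lists of primary and secondary outcomes.
- **Statistical analysis:** "All analyses will be done by a blind researcher before uncoding the study interventions".

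**The concern.** Two statements sit badly together. The analyst is to be blind until every analysis is finished, and one of the measurements to be compared between A and B is the serum level of the nutrient given to one arm only. All patients enter below 30 ng/mL, and the active arm takes the supplement for 12 weeks. If that arm's level rises as intended, the comparison itself shows which letter is active.

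Because the letter belongs to the whole arm, the damage is not confined to one patient. Anyone who learns the meaning of a letter, by whatever route, then knows the treatment of every patient whose letter they can see. Individual bottle numbers would confine such a break to one patient.

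At stake is the protection that blinding gives to decisions taken with the data in view. The Statistical analysis section makes the choice of test depend on the data (normality test, then log transformation, then a non-parametric test), across seven primary outcomes. The Exclusion criteria also allow removal after randomization, for example for antioxidant use or weight loss above 2 kg. A secondary issue is whether the next letter can be foreseen at enrolment.

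**Working it through.** **1. The plan's own figure.** Sex (2) × BMI (2) = 4 strata. 46 / 4 = 11.5 per stratum, which agrees with the stated 12 ± 1 if the strata fill evenly.

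**2. Can the analyst identify the active letter?** Suppose the analyst takes the letter with the higher end-of-trial 25(OH)D mean to be vitamin D. With true difference d, common SD s and n per arm, this is right with probability Φ( d / (s·√(2/n)) ).

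Inputs: n = 18 (Participants section). The values of d and s are assumptions, because the article gives only the entry limit of 30 ng/mL.

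| SD (ng/mL) | d = 5 | d = 10 | d = 15 | d = 20 |
|---|---|---|---|---|
| 8 | 0.970 | 0.9999 | >0.9999 | >0.9999 |
| 10 | 0.933 | 0.999 | >0.9999 | >0.9999 |
| 15 | 0.841 | 0.977 | 0.999 | >0.9999 |

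Worked corner: d = 10, s = 15 gives a standard error of 15·√(2/18) = 5, z = 10/5 = 2 and Φ(2) = 0.977. With all 23 per arm that cell is 0.988, and the d = 5 column runs from 0.871 to 0.983.

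**3. How far does one identification reach?** With one letter per arm, 46 of 46 patients. With unique numbers, 1 of 46.

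**4. Can the next letter be foreseen?** This supposes that enrolling staff know the block size and see earlier letters in the stratum. A block of four has six equally likely orders of AABB.

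- Chance that the letter is already determined, by position: 0, 0, 1/3, 1. The sum is 4/3 of 4, or 33.3%.
- Chance that the best guess (the letter with more places left) is right: 1/2, 2/3, 2/3, 1. The sum is 17/6 of 4, or 70.8%.

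For this trial, take strata of 12, 12, 11 and 11:

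- Certain: a stratum of 12 gives 3 × 4/3 = 4, and a stratum of 11 gives 2 × 4/3 + 1/3 = 3. The total is 4 + 4 + 3 + 3 = 14, and 14/46 = 30%.
- Guessed correctly: a stratum of 12 gives 3 × 17/6 = 8.5, and a stratum of 11 gives 2 × 17/6 + 11/6 = 7.5. The total is 32, and 32/46 = 70%.

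A split of 13, 11, 11, 11 gives 13 certain (28%) and 31.5 correct (68%).

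**5. Would another block size cure it?** With visible letters, a block of 6 gives 25% certain and 68% correct, and a block of 8 gives 20% and 67%. A block of 2, if recognised, gives 50% and 75%. With unique numbers and no shared letter, earlier labels carry no information: 0% certain and 50% correct, whatever the block size.

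**6. Timing.** The stated recruitment window, 15 April 2018 to 15 January 2019, is 275 days. The first patient could complete 12 weeks (84 days) with (275 − 84)/275 = 69% of the window left, or about 32 of 46 patients if intake is even. Only if vitamin D were assayed as patients finish could the meaning of the letter become known during that time.

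**The case against.** A reader might infer that allocation in this trial was predictable and that patients could be steered to an arm. The article does not support that. The figures in step 4 concern the letter, not the treatment, and the Intervention section withholds the letter's meaning from the researchers. They also need enrolling staff who know the block size and keep track of letters by stratum, while allocation is in the hands of someone outside the project. The article does not say what enrolling staff knew. It derives the block size from the sex and BMI matching, so four may even have been confused with the number of strata. This objection stands, and it makes the enrolment risk conditional.

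A reader might also infer that printing the block size gave the scheme away. The article is dated 4 March 2019, 48 days after the planned end of recruitment, so on the stated dates it could not have informed enrolment.

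Nor is it established that the blind breaks during treatment. Serum is stored frozen, which permits a single batch at the end, and the timing of the vitamin D assay is not given. If it is batched, enrolment and treatment are already over, and the exposure falls on the analyst and perhaps the laboratory.

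Finally, the 25(OH)D separation is assumed, any trial that measures the supplemented nutrient meets this difficulty, and the order of analysis steps is prescribed. That lowers the stakes. It does not rescue the analyst's blind as described, because the comparison is among the analyses to be finished before uncoding. The third person's role does not help either, since the shared letter travels on the bottle.

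**Conclusion.** The point holds in a limited form.

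- **Shared letter.** This follows directly from the text: one identification exposes 46 of 46 patients.
- **Analyst's blind.** It is unlikely to hold as described. The probability of identifying the active letter is about 0.98 or more for an assumed difference of 10–20 ng/mL, and 0.84–0.97 at 5 ng/mL (SD 8–15, 18 per arm). The difference and SD are assumptions, not figures from the article.
- **Allocation.** About 30% of next letters would be certain and about 70% guessable, but only if staff know the block size and see earlier letters within a stratum. This becomes prediction of treatment only if the meaning of the letter is also known, for example through rolling vitamin D assays.

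Nothing here shows that selection or biased analysis took place. It is a weakness that can be removed cheaply.

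**What to change.** 1. For any bottles not yet issued, the third person labels them with unique participant or kit numbers, with no letter common to an arm, and alone holds the list linking numbers to arm.
2. End-of-trial 25(OH)D and calcium are kept out of the analyst's dataset until the primary and secondary outcome models are run and locked, and are analysed afterwards. Calcium is included because the protocol itself uses it as the marker of vitamin D excess. This rule concerns the analyst's data access only.

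The second step can still be applied if every bottle has been issued. A patient enrolled on 15 January 2019 would finish 12 weeks on 9 April 2019, after the article's date. Changing the block sizes is not needed: with unique numbers it adds little, and with visible letters it does not cure the problem.

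The cost is slightly more bookkeeping: relabelling by the person who already packs the bottles, and one data-access rule. No treatment, visit or measurement changes.
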